## Abstract

**Introduction:**

In England, for babies born at 23–26 weeks gestation, care in a neonatal intensive care unit (NICU) as opposed to a local neonatal unit (LNU) improves survival to discharge. This evidence is shaping neonatal health services. In contrast, there is no evidence to guide location of care for the next most vulnerable group (born at 27–31 weeks gestation) whose care is currently spread between 45 NICU and 84 LNU in England. This group represents 12% of preterm births in England and over onr-third of all neonatal unit care days. Compared with those born at 23–26 weeks gestation, they account for four times more admissions and twice as many National Health Service bed days/year.

**Methods:**

In this mixed-methods study, our primary objective is to assess, for babies born at 27–31 weeks gestation and admitted to a neonatal unit in England, whether care in an NICU vs an LNU impacts on survival and key morbidities (up to age 1 year), at each gestational age in weeks. Routinely recorded data extracted from real-time, point-of-care patient management systems held in the National Neonatal Research Database, Hospital Episode Statistics and Office for National Statistics, for January 2014 to December 2018, will be analysed. Secondary objectives are to assess (1) whether differences in care provided, rather than a focus on LNU/NICU designation, drives gestation-specific outcomes, (2) where care is most cost-effective and (3) what parents’ and clinicians' perspectives are on place of care, and how these could guide clinical decision-making. Our findings will be used to develop recommendations, in collaboration with national bodies, to inform clinical practice, commissioning and policy-making. The project is supported by a parent advisory panel and a study steering committee.

**Ethics and dissemination:**

Research ethics approval has been obtained (IRAS 212304). Dissemination will be through publication of findings and development of recommendations for care.

**Trial registration number:**

NCT02994849 and ISRCTN74230187.

Strengths and limitations of this studyScientific evidence from this study will be used to develop national recommendations for health service delivery for babies born between 27 and 31 weeks gestation in England.This will be guided by clinical outcomes, cost-effectiveness, parents’ and staff perspectives.As a retrospective population-based observational cohort study, it is subject to selection bias in the assignment of location of birth of babies.Heterogeneity in the quality of care provided within and between local neonatal unit and neonatal intensive care unit, is likely, and will be addressed.Formal study-driven neurodevelopmental follow-up is not cost-effective in this large cohort, so routinely collected data will be used to investigate their outcomes.

## Background and rationale

Specialised services for babies in England are delivered by neonatal units managed through Operational Delivery Networks.^1^ These are geographical groupings of neonatal units working together in care pathways, and comprise units that are designated as neonatal intensive care units (NICUs), local neonatal units (LNUs) and special care baby units (SCBUs).^2 3^ There were 15 operational delivery networks (ODNs) in England in 2018.^4^ NICUs are located within centres that have specialist obstetric and fetomaternal medicine services; they have staff and resources to provide tertiary level care for babies of all gestational ages with a wide range and complexity of conditions. LNUs provide care for babies within their local catchment area; they are able to provide emergency, short-term intensive care but are not resourced to provide long-term intensive care. SCBUs provide the lowest intensity of care usually for babies born >32 weeks gestation.

Caring for babies born at 23–26 weeks gestation in an NICU improves survival to discharge. This is now shaping policy for this category of babies.^5–7^ However, there is no evidence to guide the location of care for the next most vulnerable group of babies born between 27+0 and 31+6 weeks gestation (hereafter called ‘born at 27–31 weeks’). This is an important group, accounting for around four times the throughput in neonatal units compared with those born at 23–26 weeks gestation,^8^ representing ~12% of all viable preterm babies born in England in 2013.^9^

Most ODNs have a defined gestational age cut-off, below which they aim to provide care in an NICU.^3 10^ However, these criteria differ between networks and are often not adhered to. Currently, care pathways for babies born at 27–31 weeks gestation are undefined and their management is spread, often arbitrarily between NICU and LNU. While there is some evidence to suggest that morbidity profiles (based on common major morbidities such as necrotising enterocolitis, retinopathy of prematurity and bronchopulmonary dysplasia) for the total group of babies born at 27–31 weeks gestation^6^ is similar between LNU and NICU, it remains unknown whether location of care and/or birth, makes a difference to gestation-specific outcomes. Our research will determine whether the type of neonatal unit in the hospital of birth influences outcomes for babies born at 27–31 weeks gestation, and if so, at which set point within this gestational age range care can equitably be provided in either LNU or NICU.

Presently, most pregnant women who want a hospital birth are advised to choose antenatal care and delivery in a hospital in their area,^11^ which may have NICU, LNU or SCBU facilities. With the advent of Choose and Book,^12^ this may be changing. Place of booking may also partly be determined by the anticipated degree of illness or complexity of care required for either mother or baby, if that can be predicted. However, for most women at the time of booking for pregnancy care, these risks are unknown and unpredictable. Women in threatened preterm labour at 27–31 weeks gestation will generally attend their hospital of booking for assessment or one closest to them at the time. Many will, therefore, deliver there, regardless of the type of neonatal care that can be offered. Babies that are inevitably born into an SCBU setting in this gestational age range are usually transferred ex-utero to an LNU or NICU for ongoing care. They may be returned to an SCBU from an NICU or LNU for ‘step-down’ hospital care if this is the unit closest to the mother’s home, they are usually older than 32 weeks gestation and better, but not yet ready for discharge home. Generally, transfers that do occur between hospitals, whether for a mother before delivery or for her baby after birth, and are determined by care requirements, and by cot capacity and adequacy of neonatal nurse and medical staffing.

The total healthcare, social and education costs associated to prematurity at 27–31 weeks gestation during childhood has been estimated to be £607 million in 2016.^13^ Survival in preterm babies has improved in recent years, and hospital costs are high. With neonatal intensive care averaging £1445 per day and high dependency care £925 per day^14^ in 2017/2018, it is important to ensure that care for less sick preterm babies is not unnecessarily located within an NICU, and that sicker preterm babies are not undersupported in an LNU, potentially resulting in prolonged intensive care and greater short-term and long-term morbidity. Importantly, if key clinical outcomes do not significantly differ between LNU and NICU, then cost-effectiveness and family satisfaction should be the major drivers for how and where health services are delivered.

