**Figure 2 F2:**
[figure not shown]
Overview of OPTI-PREM workstreams. BAPM, British Association of Perinatal Medicine; LNU, local neonatal unit; NICU, neonatal intensive care unit; NNRD, National Neonatal Research Database; ODNs, operational delivery network;

Workstream 1: Clinical outcomes study

Workstream 1 aims to determine whether the type (designation) of unit (NICU vs LNU) at birth influences the primary outcome (mortality) and secondary outcomes (morbidities) in babies born at 27–31 weeks gestation.

Workstream 2: study of clinical care provided in different neonatal units

Variation exists in how neonatal units manage preterm babies of all gestational ages, even among units of the same designation.^15–18^ In this workstream, we will address the secondary objective of identifying key differences in unit characteristics and clinical practices that could influence outcome. This will allow us to group neonatal units based on care provided, and to search for associations with gestation specific outcomes, irrespective of their designation.

Workstream 3: cost-effectiveness analysis

The health economics analysis investigates whether being born in settings with an NICU or LNU represent value for money within the National Health Service (NHS). A detailed cost analysis of the neonatal care received will be carried out. An incremental analysis of costs and the number of lives saved between different locations of birth will also be conducted.

Workstream 4: ethnographic study with parents and clinicians

Using an ethnographic approach that accesses their lived experiences^19 20^ of caring for these babies, this stream explores parents' and clinicians’ experiences and perspectives regarding decisions about place of care.

Workstream 5: collaboration with the British Association of Perinatal Medicine (BAPM) to establish framework documents and recommendations on place of birth.

A working group will be established in collaboration with BAPM, which will engage with relevant stakeholders, the BLISS parent advisory panel and other support groups. Its purpose will be to establish a framework document and design recommendations for place of birth for babies born at each week of gestation between 27 and 31 weeks, based on the evidence from this study.

### Workstreams 1 and 3

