#### Population

All babies born at 27–31 weeks gestation between 1 January 2014 and 31 December 2018, in an English hospital with an LNU or NICU, whose records are captured within the National Neonatal Research Database (NNRD) will be included. With approximately 6000 babies per year in England meeting our criteria, the study is expected to include data on approximately 30 000 babies. Data on births and transfers to and from an SCBU will also be captured, to provide baseline information of place of birth, care and transfer across all neonatal units in England for this gestational age range.

Data sources:

Neonatal data: The NNRD will provide data on admissions to LNU or NICU in England. The NNRD is maintained by the NDAU and created from electronic health records.^21^ It includes the information on characteristics of mothers and babies (eg, maternal pregnancy information, baby’s birth weight, sex and gestational age), admission-related episodes (eg, reason for admission, admission temperature, length of stay and the number of episodes of care) and daily neonatal care of the babies after birth (eg, treatment, clinical procedures and morbidities).Postneonatal data: To assess outcomes (survival and morbidities) to 365 days of age, the NNRD data will be linked to:Hospital Episode Statistics (HES): information all admissions, outpatient appointments and accident and emergency attendances at NHS hospitals in England.Office for National Statistics (ONS): information on location, date and cause of death, obtained from death registration records.

Neonatal units will be allowed to assess the quality of their data entry onto electronic records, based on completion of data being fed back to neonatal units for surfactant replacement, nitric oxide and discharge home on oxygen.

Inclusion and exclusion criteria: Units will be offered an opt-out option at the start of the project. The confidentiality of neonatal units who chose to opt out will be respected. A minimum dataset describing these units will only be reported if it is possible to maintain their anonymity in this process.

Clinical outcomes: The primary outcome for workstream 1 is death before discharge from a neonatal unit. We expect a within-unit mortality percentage of approximately 5% in this group. Information on deaths outside of neonatal care will be provided from ONS.

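### A non-significant LNU–NICU difference cannot support a week-by-week conclusion that either unit type will do; use a confidence-interval criterion instead

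*Protocol article*

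**What the plan says.** The last paragraph of Background and rationale links results to service policy: "if key clinical outcomes do not significantly differ between LNU and NICU, then cost-effectiveness and family satisfaction should be the major drivers" of how and where services are delivered. Earlier in the same section the study undertakes to determine whether unit type at birth affects outcomes and, if so, "at which set point within this gestational age range care can equitably be provided in either LNU or NICU".

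Both the question and its use are week-specific. The Abstract (Methods) puts the primary objective "at each gestational age in weeks". The description of Workstream 5 says that a working group will "design recommendations for place of birth for babies born at each week of gestation between 27 and 31 weeks", using this study's evidence.

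On size, the Population section gives: "With approximately 6000 babies per year in England meeting our criteria", births "between 1 January 2014 and 31 December 2018", and about 30 000 babies in all. On the primary outcome, death before discharge, it says: "We expect a within-unit mortality percentage of approximately 5% in this group". The article states no margin and no interval criterion, and the matching section says that the matched sample size cannot yet be given.

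**The concern.** Saying that care can be given equitably in either setting from some week onwards is a claim of comparability. Failing to find a significant difference is weaker evidence: it can mean that the settings are alike, or that the data could not tell them apart. Using the second as if it were the first rewards imprecision, because the wider the interval, the more easily a week passes.

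The output is meant to shape national recommendations on place of birth. If a week with an uninformative interval is read as showing no difference, the choice moves to cost and family satisfaction while a mortality or morbidity difference that matters is still compatible with the data.

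**Working it through.** **Stated figure.** 6000 per year × 5 years = 30 000, which reproduces the article's total. It is a count of available babies; the article gives no power or precision figure to check.

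**Inputs.** From the article: 30 000 babies, five gestational weeks, about 5% mortality overall. Assumed: equal weeks (30 000 / 5 = 6000 each), 1:1 allocation (3000 per group), equal true risks, two-sided 95% intervals, no matching loss, no clustering. The article gives no mortality by week, so 1% and 2% are shown beside 5%.

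**Weekly precision.** SE = √(2p(1−p)/n); half-width = 1.96 × SE; n = 3000 per group.

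| Mortality p | SE (points) | Half-width (points) | Relative to p |
|---|---|---|---|
| 5% | √(2×0.05×0.95/3000) = 0.56 | 1.10 | 22% |
| 2% | √(2×0.02×0.98/3000) = 0.36 | 0.71 | 35% |
| 1% | √(2×0.01×0.99/3000) = 0.26 | 0.50 | 50% |

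These intervals are centred on zero. An observed difference just short of significance has an interval reaching about twice the half-width: 2 × 1.10 = 2.2 points at 5% mortality (44% relative) and 2 × 0.71 = 1.4 points at 2% (71%). The article's wording would class both as not significantly different.

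**Pooled precision.** With 15 000 per group at 5%, the half-width is 1.96 × √(2×0.05×0.95/15 000) = 0.49 points. The SE of the log risk ratio is √(2×0.95/(0.05×15 000)) = 0.0503, so the interval around 1 is exp(±1.96×0.0503) = 0.91 to 1.10. The weakness is in the weekly conclusions.

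**Sensitivity.**
- 30:70 split at 5%: half-width 1.20 points (24%).
- Matching keeps half the babies: multiply by √2, giving 1.10 × 1.41 = 1.56 points at 5% and 0.71 × 1.41 = 1.00 at 2%.
- Two-stage least squares at 5%, with an assumed instrument–exposure correlation r of 0.6 to 0.3: divide by r, giving 1.10/0.6 = 1.8 to 1.10/0.3 = 3.7 points.
- Unequal weeks (assumed shares 13, 16, 18, 23 and 30%, mortality falling from 10% to 2.5%, 4.9% overall): half-widths run from 1.88 points at week 27 (19% relative) to 0.65 at week 31 (26%). With half the babies matched they run from 2.66 (27%) to 0.91 (36%).

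**What an interval criterion could achieve.** If the true difference is zero, the whole 95% interval falls inside ±m with 80% probability when m = (1.96 + 1.28) × SE. With 3000 per group, m = 3.24 × 0.56 = 1.8 points at 5% (36% relative), 3.24 × 0.36 = 1.2 at 2% (59%) and 3.24 × 0.26 = 0.8 at 1% (83%). In absolute points the criterion gets easier as mortality falls; relative to baseline it gets harder. One absolute margin for all weeks would therefore be most lenient where deaths are rarest: a 1-point margin at 1% mortality would allow a doubling.

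**The case against.** **It is rationale, not a rule.** The sentence is in the Background, names no test or alpha, and never says equivalent. The methods sections do not use significance as a criterion, and recommendations come from a working group with consultation. A reader might infer a formal decision rule that treats non-significance as proof of interchangeability; the article does not say that. What stands is that this sentence is the one stated bridge from results to policy, and the week-specific aims and recommendations give it weight.

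**Margins belong in an analysis plan.** A condensed article may leave them out, and their absence alone is no fault. The point here is the criterion that the article does state.

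**Mortality is not discarded.** The economic section uses lives saved as its health outcome and combines it with costs by net benefit, whether or not the difference is significant. It would be wrong to say that a missed mortality difference simply drops out. Morbidities are different: they are not a health outcome there and can enter only through resource use.

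**Place of birth is already the exposure.** This is correct, and the planned recommendations are for place of birth. A null by birthplace might be read as showing that care throughout in an LNU is comparable. The article does not claim this, but since it also speaks of where care is provided, a clarifying line is worthwhile.

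**The figures rest on assumptions.** They do, and instrumental variables only complement matching. Nor do the documents show that later weeks have the thinnest data, since no week sizes are given. The argument does not need this: relative precision is limited under equal and unequal weeks alike.

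**Conclusion.** The concern holds for week-specific conclusions. Under favourable assumptions (6000 babies per week, 1:1, no matching loss or clustering), a weekly interval centred on no difference still extends 22% of baseline mortality either way at 5%, 35% at 2% and 50% at 1%. A result just short of significance extends about twice as far. Matching loss and two-stage least squares widen these intervals. Week sizes, weekly mortality, allocation and instrument strength are assumed, but the conclusion holds across the ranges shown. Pooled over all weeks, the unadjusted best-case precision would support a useful statement.

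A reader might take the smallest difference detectable with 80% power (2.80 × 0.56 = 1.6 points at 5%, about 32% relative) as what the data cannot exclude. That is a different quantity; the interval half-width is the one to use here. The fault is an inference stated in the rationale and carried towards weekly recommendations. It is not a formal test procedure that has been wrongly specified.

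**What to change.** Replace the condition "do not significantly differ between LNU and NICU" with an interval criterion, for example:

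> LNU and NICU birth are called comparable at a given gestational week only if the 95% confidence interval for the mortality difference, allowing for clustering by hospital, lies within a margin fixed before outcome data are seen and set in relation to that week's expected mortality. Otherwise the week is reported as inconclusive, with its interval. Morbidities are judged by their confidence intervals, not by p > 0.05. Conclusions concern place of birth under current transfer practice.

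The steering committee and the parent advisory panel are the natural bodies to agree the margins. They should not set a single absolute margin for all weeks, for the reason shown in the working.

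The cost is one meeting and revised wording; no new data are needed. The downside is that some weeks will be declared inconclusive, particularly if the margin is tight relative to baseline or matching discards many babies.

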## Methods and analysis

### Objectives of OPTI-PREM workstreams

OPTI-PREM (Optimising neonatal service provision for preterm babies born between 27 and 31 weeks gestation in England) is a mixed-methods study comprising five workstreams. A summary of the study aims and objectives are described in figure 1 and expanded below.

**Figure 1 F1:**
[figure not shown]
Overall aims and objectives for OPTI-PREM. BAPM, British Association of Perinatal Medicine; LNU, local neonatal unit; NICU, neonatal intensive care unit; NHS, National Health Service.

### Patient and public involvement

Opti-Prem is supported by a parent advisory panel (figure 2) of representatives from BLISS, the acronym for the National Charity for babies born preterm or sick. The BLISS senior research engagement officer is part of the project’s study steering committee. The chair of the parent advisory panel is a collaborator on the project.

**Figure 2 F2:**
[figure not shown]
Overview of OPTI-PREM workstreams. BAPM, British Association of Perinatal Medicine; LNU, local neonatal unit; NICU, neonatal intensive care unit; NNRD, National Neonatal Research Database; ODNs, operational delivery network;

Workstream 1: Clinical outcomes study

Workstream 1 aims to determine whether the type (designation) of unit (NICU vs LNU) at birth influences the primary outcome (mortality) and secondary outcomes (morbidities) in babies born at 27–31 weeks gestation.

Workstream 2: study of clinical care provided in different neonatal units

Variation exists in how neonatal units manage preterm babies of all gestational ages, even among units of the same designation.^15–18^ In this workstream, we will address the secondary objective of identifying key differences in unit characteristics and clinical practices that could influence outcome. This will allow us to group neonatal units based on care provided, and to search for associations with gestation specific outcomes, irrespective of their designation.

Workstream 3: cost-effectiveness analysis

The health economics analysis investigates whether being born in settings with an NICU or LNU represent value for money within the National Health Service (NHS). A detailed cost analysis of the neonatal care received will be carried out. An incremental analysis of costs and the number of lives saved between different locations of birth will also be conducted.

Workstream 4: ethnographic study with parents and clinicians

Using an ethnographic approach that accesses their lived experiences^19 20^ of caring for these babies, this stream explores parents' and clinicians’ experiences and perspectives regarding decisions about place of care.

Workstream 5: collaboration with the British Association of Perinatal Medicine (BAPM) to establish framework documents and recommendations on place of birth.

A working group will be established in collaboration with BAPM, which will engage with relevant stakeholders, the BLISS parent advisory panel and other support groups. Its purpose will be to establish a framework document and design recommendations for place of birth for babies born at each week of gestation between 27 and 31 weeks, based on the evidence from this study.

### Workstreams 1 and 3

